#### Secondary Outcomes

Analysis of continuous secondary outcomes will be conducted in a manner similar to that used for the primary outcome. For continuous variables such as blood-based metabolic risk biomarker variables, additional Fitbit device–measured variables, and laboratory assessment variables, we will perform an ANOVA test or, if parametric assumptions are not met, a Kruskal-Wallis test. To analyze differences in categorical variables, such as smoking status and psychological variables related to T2D genetic risk communication, we will conduct chi-square tests.

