#### Secondary Outcomes

All measurements of secondary outcomes will be conducted at baseline, immediately after the intervention, 12 months after the intervention, and at the 6-month follow-up. The secondary outcomes are presented in Textbox 1.

Secondary outcomes.

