### Timing of Outcome Assessments

The time points for outcome measurements during the trial are presented in Table 1.

**Table 1 table1:** Schedule of assessments.

Assessments	Time points				
	Baseline	Immediately after the intervention	12 months after the intervention	6-month follow-up	After the follow-up
MVPA^a^ time (minutes)	✓	✓	✓		✓
Steps	✓	✓	✓		✓
Sedentary time (minutes)	✓	✓	✓		✓
Sleep time (minutes)	✓	✓	✓		✓
Lightly active time (minutes)	✓	✓	✓		✓
Fairly active time (minutes)	✓	✓	✓		✓
Very active time (minutes)	✓	✓	✓		✓
Activity calories (kcal)	✓	✓	✓		✓
Psychological variables of genetic risk communication	✓	✓	✓	✓	
PA^b^ and sitting time	✓	✓	✓	✓	
Fruit and vegetable consumption	✓	✓	✓	✓	
Smoking status	✓	✓	✓	✓	
Blood-based metabolic risk biomarkers	✓			✓	
Height (cm)	✓			✓	
Weight (kg)	✓			✓	
Handgrip strength (kg)	✓			✓	
Systolic and diastolic blood pressure (mm Hg)	✓			✓	
Resting heart rate (BPM^c^)	✓			✓	

^a^MVPA: moderate to vigorous physical activity.

^b^PA: physical activity.

^c^BPM: beats per minute.

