### Analysis Methods

#### Primary Outcome

We will perform primary outcome analysis according to intention-to-treat principles using a series of linear mixed effects models with fixed effects for time, group, and group × time interactions for objectively measured MVPA time, with repeated measures for each participant. Models will be adjusted for potential confounders such as age, sex, and BMI. Adjusted marginal means with 95% CIs will also be presented to compare differences between study groups across all assessment time points.

The analysis will use a longitudinal data analysis model to examine patterns of differences across assessment time points, study groups, and group × time interactions. Results for the group × time interaction term will be included. In addition to the 4 assessment time points, the analysis will also be performed with time as a continuous variable across the study period. The effect modification will also be investigated according to the level of T2D genetic risk, which will be further categorized based on the average T2D genetic risk estimate and educational level of the sample (ie, between college and noncollege graduates). This post hoc categorization can enable us to examine the intervention effects within each group of genetic risk. To ensure fair random assignment of participants between the groups, we will examine between-group differences in the primary outcome data, using an ANOVA test or, if parametric assumptions are not met, a Kruskal-Wallis test.

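### Continuous secondary outcomes are given two analyses with no rule for which is inferential, and the text gives blood and laboratory measures four assessments where Table 1 schedules two

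*SAP article*

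**What the plan says.** Two sentences in the SAP article, Analysis Methods, Secondary Outcomes, govern the continuous secondary outcomes.

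- The first: "Analysis of continuous secondary outcomes will be conducted in a manner similar to that used for the primary outcome". The primary analysis it points to uses "linear mixed effects models with fixed effects for time, group, and group × time interactions for objectively measured MVPA time", adjusted for age, sex and BMI.
- The second names blood biomarkers, additional Fitbit variables and laboratory variables and ends: "laboratory assessment variables, we will perform an ANOVA test or, if parametric assumptions are not met, a Kruskal-Wallis test".

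The section then turns to categorical outcomes, "such as smoking status and psychological variables related to T2D genetic risk communication, we will conduct chi-square tests".

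On timing, Outcomes, Secondary Outcomes states: "All measurements of secondary outcomes will be conducted at baseline, immediately after the intervention, 12 months after the intervention, and at the 6-month follow-up". Table 1, under Timing of Outcome Assessments, shows something else for part of the list. The row "Blood-based metabolic risk biomarkers" has two ticks, at baseline and the 6-month follow-up. So do the rows for height, weight, handgrip strength, blood pressure and resting heart rate. The Fitbit and questionnaire rows have four ticks each.

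**The concern.** A mixed model with group, time and their interaction and a one-way ANOVA or Kruskal-Wallis test answer different questions and can give different p-values. With both prespecified for the same outcome and no ranking, the report could lead with either. For the Fitbit variables, which have four assessments, the ANOVA sentence also leaves open which visit is tested.

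The second sentence also does not fit the plan's reporting promise. Statistical Principles commits to adjusted marginal means with 95% CIs at each time point and to the interaction result. A Kruskal-Wallis test supplies neither.

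The timing sentence matters because the analysis has to match the data. For blood and laboratory measures there is one post-baseline value, so a four-time-point presentation cannot be produced for them.

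**Working it through.** **1. The two analysis sentences side by side**

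| Outcomes | First sentence | Second sentence |
|---|---|---|
| Blood biomarkers | mixed model | ANOVA or Kruskal-Wallis |
| Additional Fitbit variables | mixed model | ANOVA or Kruskal-Wallis |
| Laboratory variables | mixed model | ANOVA or Kruskal-Wallis |
| Role, visit, baseline term | as for the primary outcome | none stated |
| Which one is inferential | not stated | not stated |

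The second sentence covers most of the continuous secondary outcomes. Continuous self-reported measures are not named in it.

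**2. Visit counts**

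| Outcomes | Outcomes section | Table 1 |
|---|---|---|
| Blood biomarkers, height, weight, grip, blood pressure, resting heart rate | 4 | 2 |
| Fitbit variables | 4 | 4 |
| Questionnaire variables | 4 | 4 |

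The conflict is confined to the first row. It rests on the number of ticks, so it does not depend on how the table's columns were read.

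**3. What the choice of analysis could cost**

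The plan states no precision or power figure for any secondary outcome, so there is none to reproduce. Its only correlation is 0.70, given under Sample Size for repeated MVPA measures. Carrying it to secondary outcomes is an assumption.

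With equal variance σ² at baseline and follow-up and correlation ρ, the variance of a between-group comparison is proportional to:

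- follow-up values only: σ²
- change from baseline: 2(1 − ρ)σ²
- baseline-adjusted (ANCOVA): (1 − ρ²)σ²

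Ratios to ANCOVA are therefore 1/(1 − ρ²) for follow-up only and 2(1 − ρ)/(1 − ρ²) = 2/(1 + ρ) for change.

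| Assumed ρ | Follow-up only | Change |
|---|---|---|
| 0.5 | 1/0.75 = 1.33 | 2/1.5 = 1.33 |
| 0.7 | 1/0.51 = 1.96 | 2/1.7 = 1.18 |
| 0.8 | 1/0.36 = 2.78 | 2/1.8 = 1.11 |
| 0.9 | 1/0.19 = 5.26 | 2/1.9 = 1.05 |

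**4. The same cost as power**

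Take the planned analysis sample, 355 − 71 − 36 = 248, three arms, α = 0.05 and the noncentral F distribution. The noncentrality is N·f² for follow-up-only ANOVA and N·f²/(1 − ρ²) for ANCOVA.

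At ρ = 0.7, ANCOVA has 80% power at f = 0.1416, where the noncentrality is 248 × 0.1416² / 0.51 = 9.75. Follow-up-only ANOVA has 248 × 0.1416² = 4.97 for the same effect, and its power is about 50%. Repeating this for the effect that gives ANCOVA 80% power at other correlations, follow-up-only power is 67% at ρ = 0.5 and 37% at ρ = 0.8. The result barely depends on N: at N = 87 and ρ = 0.7 it is again about 50%.

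**The case against.** The best defence is that the ANOVA sentence is a check of baseline balance. The primary-outcome section uses nearly the same wording for that purpose: "To ensure fair random assignment of participants between the groups, we will examine between-group differences in the primary outcome data, using an ANOVA test". If the secondary section echoes it, the mixed model is the only inferential analysis and nothing is lost. This is possible but weak. The primary section states the purpose and the secondary section does not. The sentence also runs straight into the chi-square tests, which are the only analysis given for categorical secondary outcomes. If the whole block were a balance check, those outcomes would have no effect analysis.

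Other parts of the defence stand, and they rule out stronger readings that a reader might infer:

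- **That the plan ignores baseline.** No baseline term is named, and the Kruskal-Wallis fallback suggests a one-way comparison. But the text does not say whether follow-up values or changes are compared, and the mixed model in the preceding sentence includes baseline as a time point.
- **That the mixed model cannot be used for blood and laboratory measures.** The plan says only that the approach will be similar, and a group-by-time mixed model can be fitted to two visits.
- **That laboratory values never scheduled at 12 months will be imputed there.** The section on sensitivity analysis and missing data does not say so.
- **That chi-square tests are wrong for the psychological variables.** The plan calls these variables categorical. Their scoring is in an appendix that is not shown.

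It is also fair that a prespecified nonparametric fallback is common practice, and that the trial's hypotheses concern MVPA only.

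**Conclusion.** Two defects hold on the text alone. Blood biomarkers, additional Fitbit variables and laboratory variables have two analyses and no rule for which is inferential. The statement that all secondary outcomes are measured at four time points contradicts Table 1 for the blood and laboratory measures, though not for the Fitbit and self-reported outcomes.

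The efficiency cost is conditional. At an assumed correlation of 0.7, the ANOVA would lose about 49% of the information (1 − 0.51) if run on follow-up values alone, and about 15% (1 − 1.7/2) if run on change scores. It would lose nothing if it is only a balance check. The documents give no correlation for any secondary outcome and do not say which of the three is meant, so none of these figures can be presented as the plan's actual loss. Neither the primary analysis nor the sample size is affected. The point should still be corrected, because the data needed for a better analysis are already being collected.

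**What to change.** 1. Remove ANOVA and Kruskal-Wallis as outcome analyses of continuous secondary outcomes. If they were meant as a baseline check, label them so.
2. Name one inferential analysis per continuous secondary outcome:
   - for outcomes measured at four visits, the mixed model, stating how baseline enters;
   - for blood and laboratory measures, ANCOVA at the 6-month follow-up adjusted for the baseline value, or the equivalent two-visit mixed model. To be equivalent, that model must hold the baseline mean common to the three arms. If baseline means are left free, the group-by-time term amounts, with complete data, to the change-score comparison.
3. Correct the sentence in Outcomes, Secondary Outcomes, so that it matches Table 1, and limit the four-time-point presentation in Statistical Principles to outcomes that have four assessments.

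The cost is a few sentences in the plan and standard code. No additional data are needed.

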### Intervention

T2D genetic risk estimates, together with a digital lifestyle leaflet, are delivered weekly via WhatsApp (Meta) and monthly via email, as results from prior studies suggest that genetic risk information can promote optimal health behavior changes when communicated at regular and repeated intervals [21,22]. A total of 113 single nucleotide polymorphisms (SNPs), with corresponding odds ratios and allele frequency values for T2D genetic risk, were derived from a genome-wide association study that identified SNPs associated with T2D risk among East Asians [23]. The estimation procedure has been illustrated in our published protocol and supplementary materials of our previous report [24,25]. Participants would then receive their estimated 10-year and remaining lifetime genetic risk for developing T2D, as well as a dichotomized genetic risk category in comparison to the average population risk for T2D (according to the participant’s age and sex): “increased genetic risk” and “no increased genetic risk.” The digital leaflet contains detailed information on the definition and health impacts of T2D, as well as lifestyle advice on 4 major T2D risk factors (ie, PA, diet, weight management, and smoking) as recommended by the World Health Organization.

Participants in intervention arm 2 receive two unique Fitbit features—(1) step goal setting and (2) activity prompts—in addition to the T2D genetic risk estimates and digital leaflet. Each participant’s step goal is set by staff to be 10% higher than their baseline step count, calculated as the average of the 7-day preintervention Fitbit data. The “Reminder to move” function is used as a prompt to interrupt prolonged sedentary periods. When the wearer has not accumulated more than 250 steps within an hour, the device vibrates and displays a reminder message. We have specified an operation period for this function, and the device reminds participants 10 minutes before each hour between 9 AM and 10 PM. All Fitbit functions unique to this intervention can be accessed and modified only by researchers via the Fitbit online dashboard system.

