### Sample Size

To ensure sufficient statistical power, we intend to recruit 355 East Asian participants with overweight or obesity. An oversampling strategy has been adopted, with 35.1% (87/248) of the full sample consisting of individuals at a higher genetic risk for T2D. The required number of participants (n=87) for subsample analysis was based on the desired medium effect size (*F*=0.3085), derived from a 3-group comparison. The control group’s average wearable device–measured MVPA time was 80 (SD 35) min/d. The intervention group receiving genetic risk information alone (intervention arm 1) demonstrated minimal changes (85 min/d), while the intervention group receiving combined genetic risk information and wearable device functions (intervention arm 2) was expected to show a difference of approximately 23% in MVPA time (105 min/d; [(105 − 85) / 85 × 100%], corresponding to a difference of 23% in MVPA time compared to previous Fitbit interventions) [26].

Our sample size calculation assumed an α level of 5%, a power of 80%, and a correlation of 0.70 among 3 repeated measures. A total of 355 participants are recruited to ensure the inclusion of an analysis sample of 248, while factoring in an expected attrition rate of 20% (71/355) and an anticipated Fitbit data missing rate of 10.1% (36/355), independent of attrition, considering instances of insufficient battery life or device loss.

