#### Safety Considerations

This is a low-risk trial and is not expected to have any major adverse effects on participants’ health. The Physical Activity Readiness Questionnaire plays a key role in identifying risk factors such as cardiovascular conditions and musculoskeletal problems. Research staff can assess participants’ health status and reduce the likelihood of injuries and other adverse events. As no adverse events are expected from participating in any of the interventions, formal monitoring of adverse events will not be conducted. However, participants may exhibit some degree of discomfort, distress, or psychological concerns regarding their genetic risk for T2D. To address this potential issue, we aim to assess participants’ psychological responses to genetic risk communication via web-based questionnaires, which will be administered at all 4 measurement time points. Participants in the intervention groups may also misinterpret genetic risk estimates. To mitigate this, representation of diabetes risk will be assessed using the Brief Illness Perceptions Questionnaire, which consists of 9 items designed to assess cognitive and emotional representations of illness. More detailed descriptions can be found in Multimedia Appendix 1 [25,27-36]. All participants are informed of the full scope and content of the study before participation and are told that they may withdraw from the study at any time without providing a reason.

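### The foreseeable harm, distress about one's genetic risk, is assessed without a split by the risk message received, so an effect confined to those told they are at increased risk is diluted in the arm comparison

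*SAP article*

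**What the plan says.** Under Safety Considerations, the SAP article states that "participants may exhibit some degree of discomfort, distress, or psychological concerns regarding their genetic risk for T2D", and answers this with measurement: "we aim to assess participants’ psychological responses to genetic risk communication via web-based questionnaires", at all four measurement time points. The same section says that "formal monitoring of adverse events will not be conducted".

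Under Intervention, both intervention arms receive numerical risk estimates and "a dichotomized genetic risk category in comparison to the average population risk for T2D", by age and sex. The two categories are "increased genetic risk” and “no increased genetic risk".

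Under Analysis Methods, Secondary Outcomes, continuous secondary outcomes are to be analysed much as the primary outcome is. The psychological variables are listed instead with smoking status as categorical: "To analyze differences in categorical variables, such as smoking status and psychological variables related to T2D genetic risk communication, we will conduct chi-square tests". No stratum, covariate or modifier is named for them.

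Under Analysis Methods, Primary Outcome, effect modification by level of genetic risk is planned for MVPA. The categories there are based on the average estimate in the sample and are called post hoc. Sample Size plans for "35.1% (87/248) of the full sample consisting of individuals at a higher genetic risk for T2D".

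**The concern.** The intervention is not a single exposure. Some participants are told something that may alarm them and the others something that may reassure them, and the harm named under Safety Considerations depends on which message was received. A comparison of arms averages over both.

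The plan already treats genetic risk as important enough to size a subsample around it and to examine MVPA by it. The same split is absent for the outcome where the content of the message matters most. At stake is the reading of a null result: an unremarkable arm-level chi-square could coexist with a clear rise in distress among those told their risk is increased.

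**Working it through.** **Inputs from the SAP article.** Analysis sample 248; higher-risk subsample 87; three arms in equal allocation (blocks of six, two per arm); each arm compared with control and with the other, with Bonferroni adjustment for pairwise comparisons.

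**The plan's own figures reproduce.**
- 355 − 71 − 36 = 248, and 87/248 = 35.1%.
- The means 80, 85 and 105 have mean 90 and SD √[(100 + 25 + 225)/3] = 10.80. Then f = 10.80/35 = 0.3086, against 0.3085 stated.
- As the between-group factor of a repeated-measures ANOVA with three measures and correlation 0.70, the smallest total with 80% power is 85. Rounded up to equal arms of 29 it is 87 (power 81.5%).

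**Assumptions, because the documents give no distress rate.** Control rate of elevated distress 20% in both risk categories; a 25-point rise in those told their risk is increased; two-sided 5%; the 35.1% share equals the share told their risk is increased, and is the same in every arm.

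**Dilution.** Net arm difference = 0.351 × rise − 0.649 × fall in the rest.
- No change in the rest: 0.351 × 25 = 8.8 points.
- A 5-point fall in the rest: 8.8 − 3.2 = 5.5 points (from unrounded values).
- Full cancellation needs a fall of 0.351/0.649 = 0.54 times the rise.

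**Power.** Normal approximation for two proportions, Φ[(d − z·SE0)/SE1], where d is the difference, z the two-sided critical value (1.96 at 5%), SE0 the standard error from the pooled proportion and SE1 that from the separate proportions.
- Unsplit, 165 v 83, 28.8% v 20%: (0.0877 − 1.96 × 0.0589)/0.0563 gives 31%.
- Stratum, 58 v 29, 45% v 20%: (0.25 − 1.96 × 0.1096)/0.0989 gives 64%.

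The same calculation under other inputs, with no change in the rest:

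| Setting | Unsplit | Within stratum |
|---|---|---|
| Arms pooled, n = 248 | 31% | 64% |
| One arm v control (83 v 83; 29 v 29) | 26% | 53% |
| One arm v control, Bonferroni for three | 14% | 35% |
| Arms pooled, n = 284 (355 − 71, attrition only) | 35% | 70% |
| Arms pooled, assumed 50% told increased | 54% | 80% |
| Arms pooled, control rate 10% | 42% | 74% |
| Arms pooled, control rate 30% | 27% | 60% |

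With a 5-point fall in the rest, the pooled unsplit power drops from 31% to 15%. The stratum figure is unaffected.

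**Precision in the stratum.** Under the base assumptions the 95% half-width is 1.96 × √(0.20 × 0.80/29 + 0.45 × 0.55/58) = 19 points with arms pooled, and 23 points with 29 in the intervention arm.

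**The case against.** The strongest reply is that this is a condensed article. The chi-square sentence does not say which groups are compared, and the instruments are described in an appendix that is not shown. If questionnaire scores were analysed as continuous, the genetic-risk split could carry over from the primary outcome. Part of this stands: an arm comparison is the natural reading, not an explicit statement. But the article does state a test for these variables and places them with the categorical outcomes, outside the carry-over. Even if the split did carry over, its cut is the sample's average estimate, whereas the message uses average population risk by age and sex. The two need not classify participants alike.

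The inputs can also be challenged. Nothing equates the planned 35.1% with the share told their risk is increased. The 248 excludes people lost for missing Fitbit data, which need not affect web questionnaires. The plan compares arms separately with Bonferroni adjustment. These points change the figures but not the direction: in every row of the table the smaller stratum is the more powerful comparison.

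Stronger readings are tempting and are not supported:
- A reader might infer that alarm and reassurance will cancel. The documents neither quantify nor exclude reassurance, so cancellation is only a possibility.
- A reader might infer that this is the trial's only safety evaluation. The section on withdrawal and loss to follow-up also reports safety-related withdrawals by randomised group at every outcome time point.
- A reader might infer that the sponsor intends to claim no psychological harm. No such claim is planned anywhere in the article.

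**Conclusion.** The point holds in a limited form. The stated analysis of the harm that the plan itself names ignores the feature of the intervention most likely to cause it, and the existing genetic-risk split does not fill the gap. If distress is confined to those told their risk is increased, the arm comparison recovers only that group's share of the effect, about 35% on the planned figures. Power for an assumed 25-point rise is then roughly half or less of that within the stratum, except at an assumed 50% share, where it is 54% against 80%.

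The distress rate, the effect size and the match between planned subsample and message category are all assumptions. The stratum comparison is better but still weak: with about 29 per arm it could not support a claim of no harm either. The change is worth making before analysis, but it does not touch the primary result.

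**What to change.** In the Secondary Outcomes part of Analysis Methods, add a comparison of the psychological variables within told category, using the same population-average cut as the message. Intervention participants told that their risk is increased are compared with controls whose own baseline estimate would have put them in that category, and likewise for the other category. Report differences with 95% CIs at each time point, beside the arm-level chi-square. State there and under Safety Considerations that a null result, at arm level or in the small increased-risk stratum, will not be taken as evidence of no psychological harm.

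No new data are needed, because genetic risk estimates are to be summarised for every arm at baseline. The cost is a few sentences and one extra table. The real downside is imprecision: with roughly 29 per arm in the increased-risk stratum, half-widths of about 19 to 23 points are to be expected under the assumptions above.

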### Randomization

A block randomization approach has been adopted. The randomization list was generated using a computer program by a staff member who had no prior knowledge of participant information. Each block consisted of 6 allocations, with 2 participants assigned to each of the 3 groups per block.

Group allocation has been concealed from study staff until the 7-day preintervention period, during which staff would have prepared the corresponding intervention materials for participants. The participants will be initially blinded to group assignment; however, blinding will not be possible once the intervention is delivered. A statistician blinded to group assignment will perform outcome analyses using deidentified data.

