### Statistical Principles

We will present 95% CIs with adjusted marginal means to compare differences between groups at each measurement time point (baseline, immediately after the intervention, 12 months after the intervention, and 6-month follow-up). Results for the interaction term will also be presented. Pairwise between-group comparisons will be performed with Bonferroni adjustment. An overall level of statistical significance will be set at α=.05 before adjustment.

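### The chi-square comparison of smoking status leaves out the baseline smoking status already recorded; it is valid but gives up some power, and conditioning on baseline is a low-priority improvement

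*SAP article*

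**What the plan says.** All places are in the SAP article.

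- **Test.** Under Analysis Methods, Secondary Outcomes: "To analyze differences in categorical variables, such as smoking status and psychological variables related to T2D genetic risk communication, we will conduct chi-square tests". The longitudinal approach is kept for other variables: "Analysis of continuous secondary outcomes will be conducted in a manner similar to that used for the primary outcome". The ANOVA or Kruskal-Wallis rule in the same paragraph is also for continuous variables. No stratified, adjusted or repeated-measures method is named for smoking.
- **Timing.** The part on secondary outcomes under Outcomes states: "All measurements of secondary outcomes will be conducted at baseline, immediately after the intervention", and then names two later time points. Table 1 ticks the row "Smoking status" at baseline and at three later time points.
- **Intervention content.** The Intervention section says the leaflet carries "lifestyle advice on 4 major T2D risk factors (ie, PA, diet, weight management, and smoking"). The Trial Design overview gives the leaflet to intervention arms 1 and 2, not to the control group. Arm 2 adds only the step goal and the movement prompts.
- **Allocation.** "Each block consisted of 6 allocations, with 2 participants assigned to each of the 3 groups per block". No stratification by smoking is mentioned, and smoking is not among the listed baseline characteristics.

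**The concern.** The question for a lifestyle intervention is whether people change: whether smokers quit and non-smokers stay non-smokers. On its natural reading, a chi-square of arm by follow-up status compares how many smokers each arm has at a visit. That count depends mostly on how many smokers the arm started with, and block allocation without stratification does not fix that number. The starting number adds noise to the comparison, although the data that would remove the noise are already collected. Two consequences follow: some loss of power to see an effect on quitting, and a result that is hard to interpret when the arms happen to differ in smoking at baseline.

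**Working it through.** **Plan's own figures.** There is no sample-size or power statement for smoking; the only calculation is for MVPA. It gives the group size used here: 355 − 71 − 36 = 248 analysed, and 248/3 ≈ 83 per arm.

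**Assumptions not in the document.** Baseline smoking p = 10%, 15% or 20%; uptake among non-smokers u = 1%; quit rate 10% in control and 20%, 30% or 40% in both leaflet arms; smoking coded yes/no; two-sided 5%.

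**Step 1: how far baseline determines follow-up.** Follow-up prevalence is p′ = p(1 − q) + (1 − p)u, and the baseline-to-follow-up correlation is φ = (1 − q − u)·√[p(1 − p) / (p′(1 − p′))]. With p = 0.15 and q = 0.10:

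- p′ = 0.135 + 0.0085 = 0.1435
- φ = 0.89 × √(0.1275/0.1229) ≈ 0.91
- 1 − φ² ≈ 0.18

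About four fifths of the variation in follow-up smoking is therefore fixed at baseline.

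**Step 2: signal against baseline noise.** With 15% smokers, quitting of 40% rather than 10% lowers follow-up prevalence by 0.15 × 0.30 = 4.5 percentage points. The chance spread of the baseline difference between two arms of 83 has SD √(2 × 0.15 × 0.85/83) ≈ 5.5 points. Only about 83 × 0.15 ≈ 12 people per arm can quit.

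**Step 3: power by simulation** (40,000 trials per setting). The plain test is the Pearson chi-square on follow-up status, 2 df. The stratified test is the generalised Cochran-Mantel-Haenszel statistic over the two baseline strata: Q = D′V⁻¹D, with Dᵢ = Σₕ(yₕᵢ − tₕnₕᵢ/Nₕ) and V the summed hypergeometric covariance, 2 df. Entries are rejection rates, plain v stratified.

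| Quit rates (control/arm 1/arm 2) | 10% smokers | 15% smokers | 20% smokers |
|---|---|---|---|
| 10/10/10% (no effect) | 4.6% v 3.2% | 5.1% v 3.8% | 5.1% v 4.0% |
| 10/20/20% | 5.2% v 5.3% | 5.8% v 7.2% | 6.2% v 8.5% |
| 10/30/30% | 6.6% v 9.6% | 8.5% v 15.0% | 10.5% v 21.1% |
| 10/40/40% | 9.7% v 16.9% | 13.8% v 28.3% | 19.1% v 41.3% |

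At 5% smokers and 10/20/20% the stratified test is slightly lower than the plain one (5.0% v 3.6%). The Fitbit missing rate need not apply to questionnaires, so the smoking analysis might have 355 − 71 = 284 people, about 95 per arm. With 10/40/40% and 20% smokers that gives 20% v 47%.

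**Step 4: chance imbalance with no true effect** (three arms, 83 each, 10% quitting throughout). A gap of 10 points or more in baseline smoking between the highest and lowest arm arises in about 7% of trials at 10% smokers and 22% at 20% smokers. Within those trials the plain test rejects in about 43% and 22% respectively, and the stratified test in 3-4%. Over all trials the plain test stays at about 5% (first row of the table).

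**The case against.** Much of the case on the other side stands.

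- **Size depends on the assumed effect.** A reader might infer that the plain test loses most of the power to detect quitting. Putting the whole effect in one arm gives a larger contrast: 10/10/40% at 15% smokers yields about 13% v 34%. The document does not support that pattern, because both intervention arms get the same smoking advice and arm 2 adds only step goals and prompts. With the effect in both leaflet arms the gain is smaller, and at modest effects it nearly vanishes.
- **The fix does not make the trial informative on quitting.** One might say that a real effect would be missed because of the chi-square. Under these assumptions it would usually be missed with the stratified test too. The main limit is the number of smokers in a trial sized for MVPA.
- **No inflation of false positives.** The imbalance point is conditional on an imbalance having occurred. It does not make the planned test invalid.
- **Other outcomes.** It would be wrong to infer that baseline is ignored throughout. The primary model has baseline as one of its four time points with a group × time term, and continuous secondary outcomes follow a similar analysis.
- **Condensed wording.** One sentence covers all categorical outcomes. The coding of smoking status and the table to be tested are not spelled out, and the questionnaire appendix is not shown. Arm by follow-up status is the natural reading, not a stated one.

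What remains is that the document names a method for smoking, the method does not use baseline status, and a better one is available from data already collected.

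**Conclusion.** The point holds as a low-priority improvement to one secondary outcome. The planned chi-square is valid, but it is less efficient than a comparison conditioned on baseline smoking and harder to read if the arms start out different. With 83 per arm, 10-20% smokers, 1% uptake and an effect in both leaflet arms, conditioning raises three-arm power from about 10-19% to 17-41% at 10/40/40% quitting and from about 7-11% to 10-21% at 10/30/30%, with almost no change at 10/20/20%. Prevalence, uptake and quit rates are all assumed, so these ranges show the order of size only. Smoking does not appear in the trial's stated objectives or hypotheses, and nothing here touches the MVPA conclusion.

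**What to change.** In Analysis Methods, Secondary Outcomes, take smoking status out of the chi-square sentence and state instead:

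- At each post-baseline visit, smoking status is compared between arms conditional on baseline smoking status, by a Cochran-Mantel-Haenszel test stratified by baseline status (exact version if smokers are few) or by a baseline-adjusted logistic or GEE model. One of these is chosen in advance.
- For each arm, report the number who quit among baseline smokers and the number who started among baseline non-smokers.
- Baseline smoking is described by arm and not tested as an outcome.

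The cost is wording only; no new data or participants are needed. There are two small downsides. Participants with missing baseline smoking status drop out of the comparison or need imputation. With few smokers the stratified test is slightly conservative (3-4% in the no-effect runs above). Because the article places formal analysis from April 2025, the change should be dated, and if smoking results by arm have already been seen it should be labelled post hoc.
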